#### Statistical analysis

Descriptive statistics will be used to report the overall park observation visitors, visitors’ characteristics, prevalence of usage of the Seniors Exercise Park, the type and level of physical activity of visitors (SOPARC). Descriptive statistics will also be used for the intercept surveys data to collate information about visitors’ perceptions about the park, motivation to use it, social connectedness/engagement with other at the park, their physical activity level and general wellbeing and their leisure/recreation activity at the park.

A generalised linear model [28] will be used to examine the effects of park refurbishment (equipment installation and site activation) on the total number of older people observed in the park, and the number of people walking and being physically active in the park. The statistical model will include terms for the intervention effect, the site effects, and seasonal effects; and overdispersion will be handled by using a quasipoisson family [32]. Statistical analyses will conducted using IMB SPSS Statistics version 26 (IBM Corporation, Armonk, NY, USA) and R [33].

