## Abstract

**Background:**

Physical activity is important to maintain health in older age, with physical activity in the outdoors providing mental and physical health benefits for all age groups. One way by which older people can engage in physical activity in the outdoors is through using suitable age-friendly outdoor exercise equipment, the Seniors Exercise Park. The ENJOY MAP for HEALTH aims to evaluate the effect of the Seniors Exercise Park installation and associated capacity building activities on park visitation, park-based physical activity by older people and delivery of community physical activity programs.

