### Study setting and partners

In this project six councils will be involved, five in metropolitan Melbourne and one in regional Victoria as follows: Knox City Council (metropolitan), Banyule City Council (metropolitan), City of Ballarat (regional Victoria), Frankston City Council (metropolitan), City of Boroondara (metropolitan), and Bayside City Council (metropolitan).

The design of the project aims for implementation in staggered stages (in three blocks, two councils per block) where each council has nominated to undergo site refurbishment in a specific timeline based on council’s site upgrade plan. Each participating council will install the Seniors Exercise Park as part of a park/site upgrade (refurbishment) in the following block allocation:

Block one: Banyule City council (Ivanhoe Park, Ivanhoe) and City of Ballarat (Mt Pleasant Reserve, Mt Pleasant).

Block two – Bayside City Council (Thomas St Reserve, Hampton) and Knox City Council (Carrington Park, Knoxfield).

Block three – City of Boroondara (Victoria Park, Kew) and Frankston City Council (Wingham Park, Frankston).

Suitable locations have been chosen with some sites planned to undergo upgrade of play space for children in addition to the installation of the Seniors Exercise Park and other amenities (e.g., water fountain, shaded area, benches). As such there will be variation between sites around the overall site size, surrounding areas and amenities, and the additional play equipment.

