##### Inclusion criteria

For the observation data collection, all park visitors will be included in the data recording. For the face-to-face intercept survey, the following inclusion criteria will be applied: (1) older adults age 60 and over, (2) adults who are able to understand basic English and have conversational English.

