### Assessments

#### Outcome measures

##### Park observation and Seniors Exercise Park equipment usage

Observation of park and exercise equipment visitation and usage will take place prior to site construction (baseline) and at two time points: one month after the site is open for public and 12 months after baseline (Fig. 2). The inclusion of two measures post-refurbishment/construction allows time for residents to become aware of the new facilities [16]. The 12 months evaluation will take place at the same time of the year as the baseline assessments to account for potential seasonal effects.

Evaluation of usage and visitations will include periodic observation (using the System for Observing Play and Recreation in Communities (SOPARC)). The SOPARC is a reliable and feasible instrument for assessing physical activity and associated contextual data in community settings [17]. It is based on momentary time sampling techniques in which systematic and periodic scans of individuals and contextual factors within pre-determined target areas in parks are made. SOPARC was designed to obtain direct information on community park use, including relevant concurrent characteristics of parks and their users. It provides an assessment of park users’ physical activity levels, gender, activity modes/types, and estimated age and ethnicity groupings. Additionally, it provides information on individual park activity areas, such as their levels of accessibility, usability, supervision, and organization. As this study focuses on the usage of the Seniors Exercise Park, we will also collect additional data (not included in the original SOPARC protocol) by coding the interaction with the outdoor exercise equipment (i.e., ‘using equipment as intended’ or ‘playing/looking/sitting’ on the equipment) [18]. We will also note the number of people moving past the equipment area without interacting with the equipment. Each site will be divided into targeted areas to be scanned. Systematic scans will be conducted over a 7-day period (Monday-Sunday) with a total of 11 scans per day as follows (22 and 55 scans for weekend and weekdays respectively): every 30 min of all park visitors in the study area during early morning (07:00–08:30), mid-day (11:30–13:00) and late afternoon (16:00–18:30) [19].

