### Statistical methods

#### Sample size estimation for intercept surveys

To our knowledge, there are no natural experimental studies that have investigated the usage of exercise equipment following an installation and site activation of specialized outdoor exercise equipment for older people. Studies investigating park visitors before and after park refurbishment (including upgrade of play spaces for children) reported an increase of 33% in park visitors (all ages combined, with 17.3% age between 21–59, and 1.8% age 60 +), with an increase of 112% engagement in moderate physical activity by children and adults [26]. An observational study conducted in NSW reported only 3.8% (*n* = 112) of all visitors utilized outdoor exercise equipment for the purpose of exercise, among these approximately 5.3% (*n* = 6) were older people [18]. Another study reported only 15.6% of park users were older people (60–70 years), with people aged 60–70 being 60% less likely to report being regular park users than the younger age groups [27].

A previous study reported approximately 3 people/visitors every 1.5 h attending a community park [16]. With 3 periods of observations/ scans and total of 5.5 observation hours (early morning, mid-day, late afternoon) per day (estimated 12 people/visitors per day), we then estimate 84 visitors for the 7-day period. Based on a previous study, approximately 15.6–17.9% are expected to be older people [26, 27], hence a sample of 15 older people (17% of 84 visitors) will be expected to be recruited per site at the baseline observation period. With an estimated twofold increase in park visitors following site activation, a sample of 30 face to face intercept interviews will be targeted at the 12 month follow up observation period at each site. With potential 18–20% declining to participate (refusal), we will aim for a total of 38 intercept interviews (13 and 25 at baseline and follow up respectively, which accounts for potential refusals) per site with an overall sample of 228 interviewees across the six sites.

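### The modelled activity outcome has no stated age limit, so activity by younger visitors could appear as an intervention effect although the aim concerns older people

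*Protocol article*

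**What the plan says.** The abstract's Background section states the aim as the effect on "park visitation, park-based physical activity by older people and delivery of community physical activity programs", and the main Background section repeats it for older people.

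The Statistical analysis section then names what the generalised linear model will be fitted to: "the total number of older people observed in the park, and the number of people walking and being physically active in the park". The first count is limited to older people; the second, "the number of people walking and being physically active in the park", refers only to people. The model has terms for intervention, site and season, with a quasi-Poisson family for overdispersion. Everything else observed in the parks is reported descriptively.

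Three other places bear on this:
- Inclusion criteria: "For the observation data collection, all park visitors will be included in the data recording".
- Park observation and Seniors Exercise Park equipment usage: SOPARC provides park users' "physical activity levels, gender, activity modes/types, and estimated age and ethnicity groupings", so age group and activity level are both available.
- Study setting and partners: "some sites planned to undergo upgrade of play space for children in addition to the installation of the Seniors Exercise Park". The number of such sites is not given.

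**The concern.** Taken as written, the only model for physical activity does not address the activity aim. That aim concerns older people, whereas the count can include children and their parents.

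The likely direction of error is favourable. A new children's play space brings in younger, active visitors at the same time as the Seniors Exercise Park opens. The protocol describes no control parks, and no model term separates the two changes, so extra activity by younger visitors is absorbed into the intervention term. The protocol's own evidence shows that such rises occur. For a refurbishment that included play spaces, it cites a 33% rise in visitors of all ages, "with an increase of 112% engagement in moderate physical activity by children and adults". A positive activity result could then be taken as a benefit to older people when none occurred.

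**Working it through.** **Inputs** (Sample size estimation for intercept surveys, unless stated)
- Expected visitors per site in the baseline week: 12 per day × 7 = 84.
- Older people among them: 15, given as 17% of 84. Arithmetically 0.17 × 84 = 14.3 and 0.179 × 84 = 15.0. The cited range for the older share is 15.6–17.9%.
- Cited rises after refurbishment: 33% in visitors of all ages; 112% in moderate activity by children and adults.
- Sites: six. Sites with a play-space upgrade: unknown, so q = 1 to 6 is shown.

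**The plan's own figures.** The Poisson coefficient of variation is 1/√15 = 25.8%, and 1.5 × 25.8% = 38.7%; both match. Simulating the quasi-Poisson model for a twofold rise in older visitors gave power of 99–100% (Poisson) and 76–95% (negative binomial), depending on the number of time points, the season term and the reference distribution. The stated power, over 80% for the negative binomial, is reproduced in most variants. It concerns older visitors only.

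**Step 1: all sites affected, older people unchanged.** Rise in the all-age count = non-older share × rise among non-older visitors. The non-older share is 1 − 0.179 = 0.821 to 1 − 0.156 = 0.844.
- 33% rise: 0.821 × 33% = 27%; 0.844 × 33% = 28%.
- 112% rise: 0.821 × 112% = 92%; 0.844 × 112% = 95%.

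Over the same data, a count restricted to older people has a ratio of 15/15 = 1.00.

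**Step 2: only q of six sites upgrade play space.** Assume equal-sized sites and no change elsewhere. Pooled rise = (q/6) × (69/84) × 112%, where 69 = 84 − 15.

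| Upgraded sites | Pooled all-age rise |
|---|---|
| 1 | 15% |
| 2 | 31% |
| 3 | 46% |
| 4 | 61% |
| 5 | 77% |
| 6 | 92% |

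**Step 3: what a full doubling would need.** The required rise among non-older visitors is (6 × 84)/(q × 69): 122% if all six sites are upgraded, 243% if three are and 730% if one is.

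**Step 4: would the model flag it?** The all-age count was simulated with 84 per site at baseline, six sites, baseline and 12 months, intervention and site terms, and 1,500 data sets per case. The negative binomial size came from the plan's variability for older visitors, 15²/((0.387 × 15)² − 15) = 12.0; carrying it over to the all-age count is an assumption. Ranges run from a t to a normal reference.
- 1.27-fold rise: significant in 88–96% (Poisson) and 21–36% (negative binomial).
- 1.92-fold rise: significant in 100% (Poisson) and 86–94% (negative binomial).

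**The case against.** The best reply is that this is shorthand. The sentence opens with older people and the aims speak of them throughout, so the second mention may simply have dropped the adjective. Nowhere does the protocol say that this outcome covers all ages. That possibility stands: the unrestricted count is the literal reading, not a declared intention. But nothing in the article narrows it, and since all visitors are recorded either count could be reported.

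A second reply is that an all-age count can be a legitimate community outcome, because the Discussion also expects other community members to benefit. This is fair, and it is a reason to keep the count under its own label. It does not make it a measure of older people's activity.

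A third is that an article leaves outcome definitions to the full plan. Here, though, the outcome is stated, and as stated it does not match the aim.

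A reader might go further and infer that children alone could double the outcome. The protocol's planning figures do not support that. Even with all six sites upgraded, 112% falls short of the 122% required, and only some sites are to be upgraded. Using the 1.8% aged 60 and over quoted from the refurbishment study would give 0.982 × 112% = 110%, but the plan's own expectation is 15.6–17.9%. The 4- to 9-fold rise cited under the targeted outcome comes from playfields used mainly for soccer and baseball, with added programming, so it does not size a play-space effect.

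**Conclusion.** The concern holds as a mismatch between the activity aim and the modelled activity outcome, with a possible favourable bias of uncertain size. The illustrations run from about +15% (one upgraded site, 112% rise) to +92–95% (all six), with about +27% from the 33% visitor rise at all sites. They rest on these assumptions:
- older people do not change;
- the visitor age mix also holds among active people;
- sites are of equal size;
- the cited 112%, which is for moderate activity in children and adults together, carries over to non-older people walking and being active.

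These are possibilities, not forecasts. The documents do not show that the activity result would mainly reflect children and parents.

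Nor should a reader infer that the trial's main hypothesis is compromised. The twofold target and the power simulation concern the number of older visitors, which is explicitly age-limited and untouched by this point. No target is set for the activity count, so a rise in it should not be compared with the targeted doubling.

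**What to change.** In the Statistical analysis section, define the modelled activity outcomes as the number of older people (SOPARC older age group) walking and the number of older people physically active. Report the all-age counts as a separate secondary result, labelled as such. Any comparison of sites with and without a play-space upgrade should be descriptive only, since there are just six sites.

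The cost is a sentence of text, smaller counts and wider intervals: active older people are a subset of about 15 older visitors per site at baseline. No new data are needed, because age group and activity level are already recorded. The restriction does not separate the Seniors Exercise Park from other parts of the refurbishment; older people who accompany children to a new play space would still be counted.

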## Discussion

The World Health Organisation Global Age-friendly Cities guide identifies outdoor space and building as one of the domains for cities and communities to deliver better outcomes for older people [34]. Age-friendly environments can foster healthy and active ageing by enabling accessible and age-appropriate safe environments. Designing age-friendly recreational outdoor spaces can promote health and health-related benefits at the population level [35–37] and promote physical activity of older people [27, 38].

The ENJOY MAP for HEALTH project is an active ageing project designed to fulfil the need for an age-friendly outdoor space for older people to support them to be physically active in the community. Interventions that involve the use of physical activity programs combined with a physical change to the built environment are likely to have a positive effect on physical activity [39]. The ENJOY MAP for HEALTH incorporates these aspects; it involves the upgrade of outdoor space with installation of specialised equipment and activities to maximise usage of the equipment by older people. Hence through our proposed four-stage process and partnership with local governments and community we aim to promote public health by combining built environment change and physical activity promotion intervention. Importantly, this project is very timely as it addresses the need for safe outdoor spaces for older people to be physically and socially active for their wellbeing. This is of particular importance in light of the anticipated recovery from the COVID19 pandemic as green space and outdoor spaces are well recognised for their importance for population wellbeing and health [40]. The project is expected to result in a significant change in the physical outdoor environment for the participating councils and communities whereby older people and other community members will be able to engage in safe physical and social activity programs, socialise more and hence improve the overall wellbeing of older people.

## Data Availability

Not Applicable.

## Abbreviations

ENJOY: Exercise interveNtion outdoor proJect in the cOmmunitY
ENJOY MAP for HEALTH: Exercise interveNtion outdoor proJect in the cOmmunitY - More Active People for HEALTHier communities
SOPARC: System for Observing Play and Recreation in Communities
WHO-5: The five-item World Health Organization wellbeing questionnaire
